### Confounders

Because of the non-randomized character of this study and the heterogeneity of patients and hospital wards, there is a risk of confounding. We will correct for a number of predefined confounders in the statistical analyses. The covariables related to *patients* are: gender, age, education, ethnicity, marital status, smoking status, body mass index, primary diagnosis, co morbidities, number of prior hospitalizations, type of admission (elective or emergent), discharge destination and the health-related quality of life at admission. *Healthcare provider factors* are gender, age, highest education, profession, years since graduation, years on the job, extent of employment, regularity of work schedules and workload. *Hospital ward characteristics* are medical specialism, hospital type, teaching status, number of admissions, bed occupancy, and number of MDs, PAs and nurses are assessed. Covariables are extracted from patient medical records and patient and care provider questionnaires.

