In this study we focus on patients admitted to a hospital, who are taken care by a hospitalist. Hospitalists are responsible for the coordination of the daily medical care of hospitalized patients [19]. This role has traditionally been fulfilled by medical residents (MRs) and occasionally by medical specialists. In recent years, the role of hospitalist has been increasingly reallocated to PAs [3,11], facilitated by technological innovations and the standardization of many medical procedures by clinical protocols [20,21]. In 2013, approximately 200 graduated PAs were employed as hospitalist in the Netherlands. When PAs are employed as hospitalists, the applied model to cover 24/7 ward care is often a mixed model that contains both PAs and MDs as hospitalist, comprising a patient medical care team. The tasks of PAs in such a team are comparable to those of the MDs. The PAs, however, tend to work during daytime on weekdays, while MDs often work during evenings, nights and weekends. It is anticipated that within the next decades PAs will be increasingly employed in the management of hospitalized patients for a range of different specialism. However, empirical evidence about the consequences of reallocating medical ward care from MDs to PAs for the quality and safety of care is currently limited.

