### Primary outcome

LoHS is the primary outcome measure. Reducing LoHs is important for payers of healthcare and for many patients. LoHS is defined as the time period in days between date of discharge and date of admission. To control for discharge delay for nonmedical reasons, i.e. delay attributable to waiting times for a place in a nursing home or a rehabilitation clinic, or help in the patient’s own home, we also register the date of completion of medical treatment in the hospital.

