### Economic evaluation

To assess the cost implications and efficiency of substitution of hospital ward care from MDs to teams with PAs, an economic evaluation is conducted alongside the outcomes evaluation. This economic evaluation is based on the general principles of a cost-effectiveness analysis, except that the time horizon per included patient is limited to one month after discharge. If equivalence of effects is established the economic decision rule alters in ‘cost minimization’. The primary cost outcome for the economic evaluation is costs associated with the principal admission (LoHS, resource use, consultation of health care suppliers, salaries, productivity loss) and costs that occurred after discharge that is potentially related to hospital ward care (unplanned readmission, presentation at emergency departments, visits of general practitioner, required home care, productivity loss) in a period from admission until one month after discharge (Table 1). The primary effect outcome in the economic evaluation is EQ-5D based QALYs. We will also analyze costs in relation to LoHS, the primary outcome in the outcomes evaluations. Besides these costs and effects, information about patient characteristics such as gender, age, primary diagnoses and co-morbidities are collected in order to account for patient case-mix as far as possible. All patient-related volumes are collected in detail at an individual patient level, primarily from medical patient records and patient and care provider questionnaires. Costs will be calculated by multiplying the volumes of healthcare use with corresponding unit prices, derived from the Dutch Manual for Costing Research [29], which also include organizational overhead costs. All figures will be related to the price level of the same year.

**Table 1 T1:** Volumes included in the economic evaluation

**Volume**	**Unit**
**During hospital stay at the included ward**^ ***** ^	
Length of hospital stay	Number of days
Non-elective transfer to ICU	Number of days
*Resource* use:	
Surgery	Type of surgery
Medication	Frequency, dose and type of medicine
Laboratory tests	Frequency and type of blood test
Radiographic imaging	Frequency and type of radiographic imaging
Scopic tests	Frequency and type of scopic test
Blood components	Number of units
Consultation with health care suppliers^‡^	Number of consultations
*Medical ward staff:*	
Hospitalists	Working hours per week hospitalist

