## Discussion

To our knowledge, this is the first multicenter study which investigates the efficacy and effectiveness of reallocation of hospital ward care from MDs to PAs. Most international studies on reallocation of care to PAs are restricted to primary or critical care, limited to one outcome measure, or are of insufficient methodological quality [2].

The major strengths of this study are the multicenter design and the broad view; we perform measurements both at patient, care provider and hospital ward level. A wide variation of instruments and methods is used to obtain data; we use both quantitative measurements (medical patient records, patient and care provider questionnaires, work schedules) and qualitative measurements (semi-structured interviews). As a consequence, we provide not only useful information about the objective effects of reallocation of hospital ward care on a range of outcomes, but we are also able to determine barriers and facilitators for the implementation.

One of the limitations is the non-randomized design of this study. In the Netherlands, PAs followed a so-called ‘dual program’, which means that students are employed within a particular medical specialty while enrolled in the master’s PA program (Table 1). After graduation, PAs are intended to be employed at the same department. The suggestion of randomly relocating the graduated PA to other hospital wards would lead to resistance among the medical specialists who put considerable effort and time to training and supervision.

The non-randomized character of this study implies an increased risk for confounding, which we will take into account in the multivariable analyses. Another challenge is to deal with the heterogeneity of patients across hospital wards. Each hospital differs slightly in determinants like the organization of ward care (care by medical resident or specialist, arrangement of supervision), policies about quality of care, patient case-mix and medical subspecialties, which might reduce explained variation and subsequently reduce the power of this study. When appropriate, we will conduct explorative secondary quantitative and qualitative analyses to explain heterogeneity.

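### The predefined confounder list for length of stay leaves out the operation for which the patient was admitted, although type of surgery is extracted for each patient

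*Protocol article*

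**What the plan says.** The Confounders section of the protocol article acknowledges the risk that comes with non-random allocation and commits to a fixed set: "We will correct for a number of predefined confounders in the statistical analyses". The patient-level items are "gender, age, education, ethnicity, marital status, smoking status, body mass index, primary diagnosis, co morbidities, number of prior hospitalizations", followed by "type of admission (elective or emergent), discharge destination and the health-related quality of life at admission". The list is enumerated without open-ended wording and names no operation or procedure. At ward level it includes medical specialism and hospital type.

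Under Data analyses, a covariable stays in the final model only if it changes the ward-model coefficient by more than 10%. That rule is the only stated route into the adjusted model, and no route is given for a variable that is not listed.

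In the Economic evaluation section, Table 1 includes surgery as a resource-use volume with the unit "Type of surgery", taken from patient medical records. The text adds: "All patient-related volumes are collected in detail at an individual patient level". The stated use is costing.

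Control wards are matched to intervention wards on medical specialism and on academic versus non-academic hospital (Study design and population). The Discussion nevertheless says that hospitals differ in "patient case-mix and medical subspecialties, which might reduce explained variation", and it relies on multivariable analysis to deal with confounding.

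**The concern.** Adjustment, together with ward matching, is this study's protection against confounding. Two wards of the same specialism and hospital type can still treat a different mix of operations, and the Discussion's remark on subspecialties points that way. Whether a patient was admitted for no operation, a minor one or a major one is a plausible determinant of LoHS, and it is settled before ward care begins. If the arms differ in this mix beyond what diagnosis, admission type and matching absorb, the difference goes into the estimated effect of the PA/MD model, in either direction. The relevant information is extracted for each patient but has no stated role in the outcome analysis.

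**Working it through.** **1. The plan's own target.** From Sample size calculation: mean LoHS 7 days, relative difference 20%, so the target is 0.20 × 7 = 1.4 days. No standard deviation is given, so the sample size cannot be strictly reproduced, but the implied SD can be found:

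- Design effect: 1 + (100 − 1) × 0.06 = 6.94.
- Patients per arm: 20 × 100 = 2000; effective number 2000 / 6.94 = 288.2.
- Implied SD at two-sided 5% and 80% power: 1.4 × √(288.2 / 2) / (1.96 + 0.84) ≈ 6.0 days.
- Standard error of the difference: 6.0 × √(2 / 288.2) ≈ 0.50 day.

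This point disputes no figure in the plan. The 1.4 days and the 0.50 day serve only as yardsticks.

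**2. What is listed against what is collected.**

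| Item | In the confounder list? | Collected? |
|---|---|---|
| Primary diagnosis, comorbidities | Yes | Yes |
| Elective or emergent admission | Yes | Yes |
| Specialism, hospital type | Yes (ward level), and matched on | Yes |
| Operation for which the patient was admitted | No | Contained in type of surgery, Table 1, but not separated from other operations during the stay |

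**3. Possible bias.** For a covariable left out of the model:

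bias = (residual effect on LoHS in days) × (residual difference in its share between the arms).

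Both inputs are assumptions, because the documents give neither. They are meant as what remains after diagnosis, admission type and matching.

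| Residual effect | Imbalance 5 points | 10 points | 20 points |
|---|---|---|---|
| 1 day | 0.05 day (4%) | 0.10 (7%) | 0.20 (14%) |
| 2 days | 0.10 (7%) | 0.20 (14%) | 0.40 (29%) |
| 3 days | 0.15 (11%) | 0.30 (21%) | 0.60 (43%) |
| 5 days | 0.25 (18%) | 0.50 (36%) | 1.00 (71%) |

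Percentages are of 1.4 days; for example 0.30 / 1.4 = 21% and 1.00 / 1.4 = 71%.

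**4. Effect on the test.** With no true effect and a bias b, the chance of a significant result is Φ(b/0.50 − 1.96) + Φ(−b/0.50 − 1.96). For b = 0.1 day this is about 5.5%, and for b = 0.3 day about 9%, against the nominal 5%.

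**5. Against the plan's own inclusion rule.** For a coefficient near the 1.4-day target, the 10% threshold is 0.10 × 1.4 = 0.14 day. Biases above that, which are most cells of the table, would bring the covariable into the model if it were on the list.

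**The case against.** The strongest defence is that the comparison already has considerable protection. Wards are matched on hospital type as well as specialism, and hospital type may separate some procedure complexity. The listed diagnosis, comorbidities, admission type, prior hospitalisations and baseline quality of life take up more. Only what is left within those matters, and since the article does not say how finely diagnosis is coded, that cannot be judged. The upper end of the range needs a 20-point imbalance and a 5-day effect to survive all of this. These points stand: they limit the size of the concern, but they do not show that the residual is nil.

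It is also fair that Table 1 records surgery during the stay on the included ward, with no stated date, indication or marker of the index operation. Some of those operations may follow from ward care, and adjusting for them could remove part of the effect under study. This stands too, and it is why the field should not be entered as it is.

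Three stronger readings are tempting and are not supported:

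- **Weekday of admission as a second omitted confounder.** The section on the primary outcome says "LoHS is defined as the time period in days between date of discharge and date of admission", so weekday can be derived, and the Background notes "The PAs, however, tend to work during daytime on weekdays". But weekday confounds only if admission days differ between matched wards, and nothing in the article suggests that they do. A weekend spent under the same kind of cover in both arms is at most a matter of effect modification.
- **Procedure as an established main driver of stay in these wards.** The article gives no data on this. It is plausible, no more.
- **A material gain in power from the added term.** The sample size calculation mentions no covariate adjustment, so any gain over a model that already holds the listed covariables and the matching cannot be derived from it.

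**Conclusion.** The point holds in a limited form. A fixed confounder list in a non-randomised comparison omits a plausible case-mix variable that is contained in data already extracted for each patient, while the article itself says that case-mix and subspecialties differ between hospitals despite matching. Under the stated assumptions the resulting bias in LoHS is 0.05 to 1.0 day. The range is wide because neither the residual imbalance nor the residual effect is documented, and the sign is unknown. It shows what could happen and is not an estimate of what will. The type I error figures also rest on an SD of about 6 days, which is inferred from the stated sample size. This is a moderate, inexpensive improvement to the adjustment set and not a flaw that invalidates the design.

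**What to change.** Add the index procedure of the admission to the patient covariables in the Confounders section, coded as none, minor or major and grouped within specialism. Include it in the adjusted LoHS model, at least as a candidate under the 10% rule in Data analyses. Define it as the operation that was the reason for admission. Exclude re-operations and operations arising from events on the ward, since ward care may influence these. Fix the grouping before the outcome comparison is seen.

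The cost is one coding rule and some recoding of a field already extracted. If the extracted field does not separate index operations from later ones, a check of the medical record is needed for the patients concerned. No new patient contact is needed, and the sample size does not change.

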### Study aim

The primary aim of this study is to determine the effectiveness of hospital ward care by MDs compared to a patient medical care team consisting of both PAs and MDs. It is hypothesized that due to reallocation of care to a fixed number of PAs per hospital ward, inpatient care becomes more standardized and continued resulting in improved care, which will be reflected by shorter hospital stay. To measure effectiveness we therefore choose length of hospital stay (LoHS) as primary outcome measure. Besides the effectiveness, also the effects on quality and continuity of care and patient and care provider experiences are investigated.

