Effects of substitution of hospital ward care on patient experienced continuity of care are measured by a set of questions in the patient questionnaire at discharge, as described in the section ‘patients experiences with medical ward care’. Additionally, continuity of care is established by evaluating work schedules. All hospitalists are asked to fill in their real work schedule during fixed weeks: week 3, 7, 11 and 15 after the start of the inclusion of patients. Continuity of care will be assessed by counting the number of rotations in the hospitalist position during these fixed four weeks. Data collection runs parallel for each pair of matched intervention and control ward.

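### The single confounder list mixes exposure components, mediators and stay-dependent ward measures with true confounders, and the 10% rule cannot tell them apart, so the adjusted LoHS estimate may not be the total effect

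*Protocol article*

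**What the plan says.** The Confounders section makes a commitment, "We will correct for a number of predefined confounders in the statistical analyses", and then gives three groups of variables without saying which outcome each group serves.

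- Patient factors end with "type of admission (elective or emergent), discharge destination and the health-related quality of life at admission".
- Provider factors include "profession, years since graduation, years on the job, extent of employment, regularity of work schedules and workload".
- Ward factors are "medical specialism, hospital type, teaching status, number of admissions, bed occupancy, and number of MDs, PAs and nurses are assessed".

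Data analyses applies one selection rule to these candidates. A covariable stays in the final model only if it shifts the coefficient of the ward care model by more than 10%, whatever its statistical significance.

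Three other sections matter here. Study setting defines the arms by who acts as hospitalist: a graduated PA covering at least 51% of weekday dayshift ward hours, or MDs alone. Study aim gives the causal argument, that "due to reallocation of care to a fixed number of PAs per hospital ward, inpatient care becomes more standardized and continued", which is expected to shorten stay. Among the secondary outcomes are hospitalist workload and a continuity measure taken from work schedules: "Continuity of care will be assessed by counting the number of rotations in the hospitalist position during these fixed four weeks".

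**The concern.** A confounder influences both which care model a ward has and how long its patients stay, and is not itself produced by the care model. Several listed variables do not fit that description for LoHS. Conditioning on a variable that carries the effect, or that is partly built from the outcome, takes away some of the effect being estimated. Conditioning on a near-copy of the exposure leaves little information with which to estimate it.

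The selection rule gives no protection. It asks only whether the coefficient moves, and mediators and exposure proxies move it at least as readily as confounders do. In a non-randomised study the adjusted estimate carries the conclusion. A real reduction in stay could be reported as small or absent because of the adjustment set.

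**Working it through.** **Step 1. Each doubtful variable against the protocol's own text.**

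| Variable | What the protocol says elsewhere | Role for LoHS |
|---|---|---|
| Number of PAs | Control wards have MDs only (Study setting), so it is 0 in every control ward and at least 1 in every intervention ward | Component of the exposure |
| Profession | PA or MD as hospitalist is the contrast under study | Component of the exposure |
| Regularity of work schedules | A fixed set of PAs is the stated route to continuity and shorter stay (Study aim) | On the causal path; close to the rotation count but not the same measure |
| Workload | Secondary outcome (patients per day, overtime) | Can be affected by the care model |
| Bed occupancy | Occupancy = admissions × mean stay / (beds × days) | Can contain LoHS if measured under the care model |
| Number of admissions | Same identity | LoHS-dependent jointly with occupancy, or alone if beds are always refilled |
| Discharge destination | Settled at discharge; waiting for a place prolongs stay (Primary outcome) | Arguable: after admission, but also carries case-mix |

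**Step 2. Scale for an illustration.** Sample size calculation gives 20% of 7 days = 1.4 days, ICC 0.06, and 40 wards of 100 patients. No SD is stated, so it is back-solved. Design effect = 1 + 99 × 0.06 = 6.94. Effective n per arm = 2000 / 6.94 = 288.2. With two-sided alpha 5% and power 80%, SD = 1.4 / [(1.96 + 0.84) × √(2/288.2)] ≈ 6.0 days. The ward-level SE of the crude difference is then √[2 × (0.06 × 36 + 0.94 × 36/100)/20] = √0.250 = 0.50 days.

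**Step 3. Number of PAs.** Assume 1, 2 or 3 PAs with equal chance in intervention wards and 0 in controls.

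- Within-arm variance, averaged over arms = ½ × 2/3 = 1/3. Between-arm variance = ¼ × 2² = 1. So r² = 1/(1 + 1/3) = 0.75, the variance inflation factor is 1/(1 − 0.75) = 4, and the SE is multiplied by √4 = 2.
- Simulation agrees: mean estimate about −1.4, SE 1.02 against 0.50, rejection about 27% against 78%.
- The 10% rule still keeps the variable. Adding it shifts the estimate at random with SD about √(1.02² − 0.50²) = 0.89 days, against a threshold of 0.14 days. A larger shift than that has probability of about 0.87; the simulated figure is 86–88%.

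**Step 4. Mediator and ward measures.** 40 ward means, true effect −1.4 days, 2000 runs per scenario. All inputs beyond Step 2 are assumed.

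| Added to the model | Adjusted effect (days) | Kept by the 10% rule |
|---|---|---|
| Schedule regularity carrying half of the effect | about −0.71 | 94% |
| Schedule regularity carrying all of it | 0.00 | 100% |
| Occupancy, responding to stay | −0.06 to −0.85 | 95–100% |
| Occupancy and admissions, same set-up | −0.05 to −0.39 | 99–100% |

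The ranges come from varying how much bed numbers and admissions differ between wards.

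**Step 5. Dependence on how wards fill.** The regime changes which variable does the damage.

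- Beds always refilled, so admissions follow stay: admissions alone gives about −0.70, occupancy alone −1.39 (no bias), both −0.63. Adding nurse numbers as a stand-in for ward size took one such simulation from −1.43 to −0.27.
- Admissions set by demand: admissions alone gives −1.39 and is kept in 8% of runs; occupancy gives −0.51.
- Both measures unaffected by the care model: no bias in any model.

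**The case against.** The strongest reply is that the list names candidates, not a fitted model, and that it serves many outcomes. Provider age, profession and years in post are ordinary covariates for job satisfaction or the GHQ-12, and allocating covariables to outcomes is a detail that an article may leave to the analysis plan. This stands in part: those factors have a legitimate use for provider-level outcomes. It does not answer the point for LoHS, because the text commits to correcting for one undivided list and states a selection rule with no step that excludes mediators or exposure proxies.

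The algebra is also open to challenge. The number of beds is not listed and the measurement period is not given, so stay cannot be reconstructed exactly from the listed ward variables. That stands; Step 5 shows that the consequence depends on when and how those variables are measured.

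Finally, strict exclusion has a price. MD and nurse staffing, patient volume and discharge destination may carry real ward-level confounding or case-mix, and specialism and hospital type are already matching factors. This also stands, and argues for sensitivity analyses rather than deletion.

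A reader might infer that adjustment will remove the effect, or that about 80% of it would go (−1.43 to −0.27 is 1 − 0.27/1.43 = 81%). The documents support neither. Entry is conditional on the 10% rule, number of PAs inflates the SE without pulling the mean toward zero in the simulation, and the 80% figure belongs to one assumed scenario.

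**Conclusion.** The concern holds as a risk built into the stated rule, not as a certain loss of effect. Number of PAs, profession, regularity of work schedules and workload are not suitable adjustment variables for a total effect on LoHS. Bed occupancy, and admissions jointly with it, are unsuitable if measured while the care model operates. The 10% rule cannot screen these out and tends to retain them where they carry or mimic the effect.

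Mediators and stay-dependent measures can attenuate the estimate; number of PAs can roughly double its SE. The doubling assumes 1 to 3 PAs per intervention ward. The attenuation, from none to most of the 1.4 days, rests on assumed mediation shares, bed numbers, filling regimes and concurrent measurement, and cannot be narrowed from the documents.

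**What to change.** State eligibility by outcome before the 10% rule is applied. For LoHS and the other patient-level effectiveness outcomes:

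1. Make number of PAs, profession, regularity of work schedules and workload ineligible.
2. Allow bed occupancy and number of admissions only if measured before the PA/MD model was in place on the ward.
3. Restrict the candidates to patient factors settled by admission and ward features that the care model does not affect, such as specialism, hospital type and teaching status.
4. Report models that add the excluded variables, and models with discharge destination or MD and nurse staffing, only as labelled mediation or sensitivity analyses.

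Provider factors, profession included, may remain covariates for provider-level outcomes. The date of completion of medical treatment, already recorded, can address placement delay without conditioning on destination.

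The cost is wording; all data are still collected. The downside is somewhat less ward-level adjustment in the primary model, which the sensitivity analyses cover.
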